### Assignment of interventions

#### Randomization

Participants will be randomly assigned to treatment group and control group at a ratio of 1:1, with 103 cases in each group. The random sequence was generated by an independent statistician, using the SAS 9.2 software.

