### Outcomes

#### Primary outcomes

Because the objective of this study is to investigate the efficacy of Qingpeng ointment for relieving pain and swelling of joints in patients with AGA, changes in joint pain severity (measured using VAS), joint swelling degree (measured using VAS), and width and thickness of affected joints (measured using vernier calipers) between baseline and treatment completion will be considered as the primary outcomes.Joint pain: Degree of joint pain will be measured by participants, using a visual analogue scale (VAS, 0–10 points, 0=no pain, 10=intolerable pain), at baseline, every day during treatment, and after 7-day treatment.Joint swelling:2.1 The width and thickness of each affected joint will be measured using vernier calipers (brand: Ruineng, model: NR0139) at baseline, every day during treatment, and after 7-day treatment.2.2 Degree of joint swelling will be measured by participants, using a visual analogue scale (VAS, 0–10 points, 0=no swelling, 10=intolerable swelling), at baseline, every day during treatment, and after 7-day treatment.

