### Statistical analysis

Statistical analysis will be performed using SAS 9.2 software, with a statistical significance of *p* value less than 0.05. Normally distributed continuous variables will be described using mean ± standard deviation (SD), and non-normally distributed continuous variables will be described using median and interquartile range (IQR). Categorical variables will be described using frequencies and percentages. Primary outcomes will be analyzed according to the intention-to-treat principle. Intra-group differences of continuous variables will be tested for significance using paired-samples *t* test when the data is normally distributed, and will be tested using non-parametric test when the data is non-normally distributed. Between-group differences of continuous variables will be tested for significance using independent-samples *t* test when the data of the two groups are normally distributed and have equal variance, and will be tested using non-parametric test when the data of the two groups are non-normally distributed or have unequal variances. Chi-square test will be used for categorical data. Data from participants who drop out from this study will be implemented by the last-observation-carried-forward (LOCF) method. Interim analyses will not be performed. For the co-primary endpoints, Bonferroni correction will be performed to correct multiplicity.

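### The caliper swelling primary outcome is defined per joint, but its between-group test needs one independent value per patient and the protocol does not say what that value is

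*Protocol article*

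**What the plan says.** Under Primary outcomes, the article lists changes in "width and thickness of affected joints (measured using vernier calipers) between baseline and treatment completion will be considered as the primary outcomes", alongside the pain and swelling VAS scores. The itemised definition then fixes the unit of measurement: "The width and thickness of each affected joint will be measured using vernier calipers". The two VAS items are described as a degree scored by the participant; only the caliper item is tied to each joint.

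More than one joint per patient is foreseen. The exclusion for skin ulceration is worded to cover one or several joints, the outcome and intervention sections speak of joints in the plural, and the inclusion criteria set no limit on joint number.

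Allocation is by person: "Participants will be randomly assigned to treatment group and control group at a ratio of 1:1, with 103 cases in each group".

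Statistical analysis gives one rule for all continuous outcomes: "Between-group differences of continuous variables will be tested for significance using independent-samples" t test when the data are normal with equal variances, and otherwise a non-parametric test. It adds "Primary outcomes will be analyzed according to the intention-to-treat principle" and "For the co-primary endpoints, Bonferroni correction will be performed to correct multiplicity". It names no index joint, no mean, sum or maximum over joints, and no model for several measurements within a patient. Baseline enters only through the change score.

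**The concern.** A two-sample t test or a rank test is valid here when each randomised patient supplies one value. The caliper outcome as defined supplies as many values as the patient has affected joints, and nothing links the two. What is compared per patient is part of the definition of a primary outcome, and it is left open.

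If the joint-level data set were passed straight to the named test, correlated changes from one patient would count as separate evidence and the standard error would be too small. With Bonferroni correction, a positive result on one endpoint can support the efficacy claim, but only if each component test keeps its own level. The non-parametric fallback would not help, because it also assumes independent observations.

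A second difficulty is scale. Affected joints can differ greatly in size, and the plan compares raw caliper changes with no adjustment for the baseline dimension.

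**Working it through.** The plan gives no figure on this point. Its sample sizes (82 per group for pain, 27 for swelling, before dropout) come from a responder proportion and a 0–3 swelling score. Neither uses caliper data or joint counts, so nothing below changes them.

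**Inputs from the protocol article**
- 103 patients per group (Randomization).
- Significance level 0.05, sidedness not stated (Statistical analysis); two-sided is assumed here.
- Bonferroni correction with the number of endpoints not given in that section; two are assumed for the 2.5% level.

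**Inputs assumed, because the document gives none**
- Number of affected joints k per patient: three mixes of 1, 2 and 3 joints.
- Within-patient correlation of caliper change (ICC): 0.3, 0.5 and 0.8.

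**Formulas**, for the case in which every joint enters as its own observation
- Design effect with unequal joint counts: DE = 1 + (E[k²]/E[k] − 1) × ICC.
- Actual two-sided error: 2 × (1 − Φ(z/√DE)), with z = 1.96 at nominal 5%.

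**One case in full.** Mix 85/10/5%: E[k] = 0.85 + 0.20 + 0.15 = 1.2. E[k²] = 0.85 + 0.40 + 0.45 = 1.7. The ratio is 1.417. At ICC 0.3, DE = 1 + 0.417 × 0.3 = 1.125, z/√DE = 1.96/1.061 = 1.848, and the actual error is 0.065.

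| Patients with 1/2/3 joints | Mean joints | E[k²]/E[k] | DE at ICC 0.3 / 0.5 / 0.8 | Actual error at nominal 5% |
|---|---|---|---|---|
| 100/0/0% | 1.0 | 1.000 | 1.00 / 1.00 / 1.00 | 5.0% throughout |
| 85/10/5% | 1.2 | 1.417 | 1.125 / 1.208 / 1.333 | 6.5% / 7.5% / 9.0% |
| 70/20/10% | 1.4 | 1.714 | 1.214 / 1.357 / 1.571 | 7.5% / 9.3% / 11.8% |
| 50/30/20% | 1.7 | 2.059 | 1.318 / 1.529 / 1.847 | 8.8% / 11.3% / 14.9% |

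At a nominal 2.5%, the three multi-joint mixes give 3.5% to 5.2%, 4.2% to 7.4% and 5.1% to 9.9%.

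**Check by simulation** (103 patients per arm, 6,000 runs per scenario, no treatment effect). Joint-level t tests at nominal 5% rejected in 6.3% to 14.9% of runs across the three multi-joint mixes, within about 0.2 percentage points of the formula. With the mean over joints as one value per patient, rejection was 4.6% to 5.6% in every scenario. The Monte Carlo standard error at 5% is √(0.05 × 0.95/6000) = 0.28 percentage points, so this is compatible with the nominal level.

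**The case against.** The strongest reply is that the article never makes the joint the unit of analysis. Measuring each joint is an instruction for data collection. Randomisation, sample size, intention-to-treat and the handling of dropouts are all framed by participant, and naming a two-sample t test between randomised groups ordinarily presupposes one value per participant. How several joints become one number could sit in an analysis plan or full protocol that is not shown. The inflation figures rest wholly on assumed joint counts and correlations, and if nearly all patients have a single affected joint the problem nearly vanishes.

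Most of this stands. A reader might infer that the trial will count correlated joints as independent and that its type I error will rise. The text does not support that: it is equally consistent with one value per patient, and the figures are conditional. Nor does it support a suspicion that a joint will be picked after the data are seen; no such procedure is described.

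What does not stand is that this is only missing detail. The article states a per-joint primary outcome and a test that needs independent values, and for a patient with several affected joints these do not fit without a rule. The same section commits itself on the test, the normality rule, dropout imputation and multiplicity, so the analysis is already fixed at this level.

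**Conclusion.** The point holds as a mismatch in the definition of a primary outcome. The caliper measure is per joint, patients may have several affected joints, patients are randomised, and the named tests need one independent value each, yet no patient-level value is given. Raw changes from joints of different size would also be compared without baseline adjustment.

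The size is conditional. If joints were entered separately, a nominal 5% test could run at about 6.5% to 15% under an assumed mean of 1.2 to 1.7 joints and an ICC of 0.3 to 0.8. If one value per patient is analysed, or every patient has one affected joint, there is no inflation. The document does not show which applies. The point should be settled before unblinding.

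**What to change.** Before unblinding, define one value per patient for width and likewise for thickness, from data already collected. An example is the mean change from baseline to treatment completion over the joints affected at baseline. Fixing the set of joints at baseline means that it cannot depend on response. Compare groups with a regression model that includes treatment and the patient's baseline caliper value averaged over the same joints, which also takes account of differing joint size. Joint-level data can be reported in a supportive mixed model with a patient random effect.

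An index joint should not be derived from baseline pain scores unless pain was recorded per joint; the article describes only a degree of joint pain and does not show that it was. The pain and swelling VAS definitions can stay as they are.

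The cost is about one sentence in the outcome definition and one in the analysis section, plus the amendment steps that the Ethics section describes. No new measurements and no change in sample size are needed. The downsides are slightly more analysis work and the chance that averaging dilutes an effect concentrated in the worst joint.

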#### Secondary outcomes

Secondary outcomes include changes in joint mobility degree and redness degree between baseline and treatment completion, changes in C-reactive protein and serum uric acid between baseline and treatment completion, and the remaining amount of rescue medicine at treatment completion.Joint mobility: Degree of joint mobility will be measured by participants, using a 0–4 points scale (0=the mobility is normal, and is not restricted; 1=the mobility is slightly restricted, but normal activities can still be performed; 2=the mobility is moderately restricted, patient is unable to perform general activities, but is able to take care of self daily life; 3=the mobility is severely restricted, pain is unbearable when the joint moves, patient is unable to take care of self daily life; 4=the joint is unable to move), at baseline, every day during treatment, and after 7-day treatment.Joint redness: Degree of joint redness will be measured by participants, using a 0-3 points scale (0=the skin color is normal; 1=the skin is slightly red; 2=the skin is obviously red; 3=the skin is dark red), at baseline, every day during treatment, and after 7-day treatment.C-reactive protein: Will be measured from a blood sample taken at baseline and after 7 days of treatment.Serum uric acid: Will be measured from a blood sample taken at baseline and after 7 days of treatment.Remaining amount of rescue medicine: Will be recorded after 7 days of treatment.

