### Sample size estimation

This study includes two primary outcomes: joint pain and joint swelling. Sample size was estimated based on these two primary outcome measures. Estimation according to joint pain was based on results from a previous study [23]. In this study, 47% participants in treatment group (Qingpeng ointment plus diclofenac sodium tablets) had significant relief of joint pain (the score of joint pain degree measured by a self-developed scale reduced by 6 points), and 25% participants in control group (diclofenac sodium tablets) had significant relief of joint pain. On the basis of a 5% type I error rate (*α*=0.05) and a power of 90% (*β*=0.1), the sample size of each group was 82. Assuming a 20% dropout rate, a total of 206 participants should be recruited, with 103 participants in each group.

Estimation according to joint swelling was likewise based on results from another previous study [19], which established score of joint swelling measured by a 0–3 points scale as 0.45 points after receiving Qingpeng ointment plus etoricoxib tablets, and the estimated standard deviation is 0.37. Score of joint swelling after receiving vaseline plus etoricoxib tablets is 0.87, and the estimated standard deviation is 0.64. On the basis of a 5% type I error rate (*α*=0.05) and a power of 90% (*β*=0.1), the sample size of each group was 27. Assuming a 20% dropout rate, a total of 68 participants should be recruited, with 34 participants in each group.

Based on these results, we chose the larger sample size of 206 participants, with 103 participants in each group.

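### If C-reactive protein is right-skewed and falls in both arms, the planned unadjusted test on its change from baseline can lose much of its power; log-scale ANCOVA would recover it (minor)

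*Protocol article*

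**What the plan says.** The Secondary outcomes section of the protocol article defines this outcome as "changes in C-reactive protein and serum uric acid between baseline and treatment completion". On timing it adds: "C-reactive protein: Will be measured from a blood sample taken at baseline and after 7 days of treatment". There is thus one baseline value and one later value per patient.

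The Statistical analysis section gives one rule for all continuous variables. Groups are compared by an independent-samples t "test when the data of the two groups are normally distributed and have equal variance"; otherwise the comparison "will be tested using non-parametric test when the data of the two groups are non-normally distributed or have unequal variances". It names no transformation and no adjustment for baseline.

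The article gives no unit, mean, SD, expected fall or expected effect for CRP. The Sample size estimation section covers joint pain and joint swelling only.

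**The concern.** The Outcomes section uses the same word, changes, for the visual analogue scores, caliper readings, short ordinal scores, urate and CRP. Subtraction is the natural reading for all of them. For a marker that varies by multiples, subtraction is a poor scale. A fall from 100 to 20 scores -80 and a fall from 10 to 2 scores -8, although each is an 80% fall. If both arms fall, ordering patients by the difference mostly orders them by where they started. Moving from the t test to a rank test on the same difference does not remove this.

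What is at stake is sensitivity, not validity. CRP is the only laboratory marker of inflammation in the trial, beside pain and swelling scores that patients give themselves. A null CRP result from an insensitive analysis could be taken as evidence against an anti-inflammatory effect when it is not.

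**Working it through.** **The plan's own figure.** For joint pain (47% v 25%, 90% power), 2 × 0.36 × 0.64 × (1.645 + 1.282)² / 0.22² = 81.5, so 82 per group. With 20% dropout, 82 / 0.8 = 102.5, so 103. The 82 reproduces with a one-sided 5%; the same formula two-sided gives 100.04, so 101. These figures say nothing about CRP. They are used here only to fix the evaluable number at 82 per group.

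**Inputs for CRP (all assumed, none in the article).** CRP is log-normal with the same log-SD (0.8, 1.0 or 1.3) at both times, and the log-scale correlation is 0.5. The active-to-placebo ratio of Day-7 geometric means is 0.65. The placebo Day-7 level is 20%, 40% or 100% of baseline, i.e. a fall of 80%, 60% or none. Tests are two-sided at 5%. The baseline median is 30; without an assay limit the unit and median do not affect the power.

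**Mechanism, at log-SD 1.0 and a 60% fall.** A placebo patient at the median goes from 30 to 12, a change of -18. On active the Day-7 value is 12 × 0.65 = 7.8, a change of -22.2, so treatment moves the difference by 4.2. A placebo patient one log-SD above the median starts at 30e = 81.5 and has a median Day-7 value of 12e^0.5 = 19.8, a change of about -61.8. One SD of baseline therefore moves the difference by about 44, roughly ten times the treatment effect. In simulation without a treatment effect, the rank correlation of the difference with baseline is -0.79 here, -0.93 at an 80% fall and -0.45 with no fall.

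**Power on the log scale, closed form.** The effect is ln 0.65 = -0.431, and √(2/82) = 0.156.
- Log ratio, log-SD 1.0: SD = 1.0 × √(2(1 - 0.5)) = 1.0; 0.431 / 0.156 = 2.76; power = Φ(2.76 - 1.96) = 79%.
- Log ANCOVA, log-SD 1.0: SD = 1.0 × √(1 - 0.5²) = 0.866; 0.431 / 0.135 = 3.19; power = Φ(1.23) = 89%.
- Log ANCOVA, log-SD 0.8: power 98%. Log-SD 1.3: power 69%.

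**Power of the rank test on the simple difference, simulated.** Under these log-normal inputs the article's rule leads to the rank test in essentially every run.

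| Placebo fall | Rank test, log-SD 0.8 to 1.3 | Repeat, 4,000 replicates per cell | Log ANCOVA |
|---|---|---|---|
| 80% | about 10–12% | 10–13% | about 69–98% |
| 60% | about 19–32% | 19–34% | about 69–98% |
| none | about 42–79% | 40–82% | about 69–98% |

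The two sets differ by at most 3 points, which is simulation error. Type I error is near 5% for every method.

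**Scale or test?** At log-SD 1.0 and a 60% fall, the same Mann-Whitney test has 76% power on the percent change, against 27–29% on the simple difference. The scale makes the difference.

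**Where the loss disappears.** With near-normal CRP (baseline mean 60, Day-7 mean 40, SD 12, correlation 0.5) and an additive effect of 6, the article's rule has 88% power and log ANCOVA 91%.

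**Assay limit and dropouts (log-SD 1.0).**
- With an assumed floor of 5 mg/L and a 60% fall, power is 23% for the rank test, 61% for the log ratio and 84% for log ANCOVA. At an 80% fall it is 8%, 31% and 74%.
- With last observation carried forward, a dropout enters with the baseline value. Taking 21 of 103 per group (about 20%) and a 60% fall, power is 22%, 70% and 78%.
- With both together at an 80% fall, the rank test has 3% and log ANCOVA only 26%. Log ANCOVA stays ahead, but its advantage shrinks.

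**The case against.** The strongest reply is that the article never says raw, absolute or mg/L. A reader might infer that the protocol has fixed a raw mg/L change, but the text gives no unit or scale, and a log difference would not contradict it. The scale of a secondary laboratory variable may well be set in an analysis plan that is not shown. This stands as a limit on the wording. It does not remove the point, because the article does state an outcome and a test for it, and neither includes a ratio scale or a baseline covariate.

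Second, every CRP input is assumed, and the provision for non-normal data is a general rule that says nothing about CRP. This also stands, so the loss has to be given as a conditional range. A fall in both arms is nevertheless plausible: patients enter within a week of onset of an acute flare, and both arms have rescue diclofenac.

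Third, a rank test is a valid way to handle skew. True: type I error holds. The rank test recovers part of the power that a t test on the difference would lose, but the figures above already credit it with that.

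Fourth, the outcome carries little weight. CRP is secondary and unpowered, and the Objectives section names only mobility, redness and safety as secondary aims. Caliper width and thickness, a primary outcome, are also instrument readings and are taken at the hospital visit as well as by patients at home. This stands and sets the severity.

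**Conclusion.** The point holds as a minor, conditional one. If CRP is right-skewed, treatment acts proportionally and levels fall in both arms, the planned rank test on a simple difference has about 10–32% power for a 35% lower Day-7 geometric mean when placebo CRP falls 60–80%, against about 69–98% for log ANCOVA. With no fall in the placebo arm it has 42–79%. With near-symmetric CRP and an additive effect the two are about equal. These figures assume 82 evaluable per group, correlation 0.5, log-SD 0.8 to 1.3 and a two-sided 5% test; an assay floor or carried-forward dropouts lower the power of log ANCOVA too.

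Two stronger readings are not supported. One is that the outcome loses most of its power outright: the article has no CRP data to show that, and it is true only in part of the range. The other is that the trial's one objective measure of inflammation is compromised: the calipers are instruments too, and CRP is more exactly the only laboratory marker. No stated power is lost, the test is valid, and the primary conclusions are unaffected.

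**What to change.** In the Statistical analysis section, state that log(Day-7 CRP) will be analysed by ANCOVA with treatment group and log(baseline CRP) as terms, that values below the assay limit will be set to one fixed value, and that the result will be reported as the between-group ratio of geometric means with its 95% CI. ANCOVA is preferable to a t test on the log ratio: it has more power in the main case (89% v 79%) and holds up better near an assay floor (74% v 31% in the worse floor case above).

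The cost is one or two sentences, settled before unblinding. It needs no new data, visits or patients. If an analysis plan that is not shown already specifies this, only the article's wording needs to be brought into line.

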**Methods:**

This study is designed as a multi-center, randomized, double-blind, placebo-controlled trial. Two hundred and six adults with acute flare of gout, and visual analogue scale (VAS) score of joint pain ≥ 3 points will be recruited. Participants will be randomly assigned to herbal treatment or placebo group at a ratio of 1:1. Qingpeng ointment, or equal placebo ointment, will be applied topically at involved joints twice a day for consecutive 7 days. Patients in both groups would be allowed giving diclofenac sodium sustained-release tablets as rescue therapy when VAS score of joint pain ≥ 7 points during the treatment. The primary outcomes will be joint pain measured by VAS score, and joint swelling measured using width and thickness of affected joints and VAS score. Other outcome measures will be joint mobility, joint redness, C-reactive protein, serum uric acid, and the use of rescue medicine as well as adverse effect.

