#### Treatment period

Patients in the treatment group will be treated with Qingpeng ointment, and patients in the control group will be treated with placebo ointment. Patients in both groups will be given diclofenac sodium sustained-release tablets (DSSRT) as rescue medicine. Drugs for other underlying diseases such as antihypertensive drugs, hypoglycemic drugs, and hypolipidemic drugs are permitted to be taken during the treatment period. And other Chinese patent medicine are prohibited during the trial. When participants experience severe skin allergies at application site, or experience serious adverse events, investigators will advise them to discontinue using the study drug. The degree of joint pain, swelling, redness, and mobility will be scored and recorded on patient diary every day by patients, and the width and thickness of affected joints will also be measured and recorded every day by themselves. The course of treatment is seven days.

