#### Treatment visit

After 7 days of treatment, participants will return to hospital for treatment visit. General physical examination and laboratory tests (including serum uric acid, C-reactive protein) will be conducted. The degree of joint pain, swelling, redness, and mobility will be scored, and the width and thickness of affected joints will be measured. The combined medication and adverse events during treatment period will be recorded. The remaining study drugs will be recovered, drug distribution and recovery record form will be filled in, and the remaining amount of Qingpeng ointment/placebo ointment and rescue medicine will be recorded.

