#### Rescue medicine

DSSRT (produced by Beijing Novartis Pharmaceutical Co., Ltd; specification: 75mg/tablet, 10 tablets/box) will be given to participants in both treatment group and control group as rescue medicine. Patients in both groups are recommended to take the rescue medicine only when the VAS score of joint pain is ≥ 7 points (scale of 0 to 10), which is scored by patients themselves. Patients will also be recommended not to take the rescue medicine when joint pain is reduced to a tolerable extent (VAS score reduce to less than 7 points). The recommended dose is one tablet per time, once daily, and the maximum dose is one tablet per time, twice a day.

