To the best of our knowledge, this study is the first multi-center, randomized, double-blind, and placebo-controlled clinical trial to assess the efficacy of Qingpeng ointment for AGA. In terms of outcome selection, considering from the perspective of patients, we chose joint pain and joint swelling as primary outcomes, and joint mobility, joint redness, remaining amount of rescue medicine, C-reactive protein, and serum uric acid as secondary outcomes. Different from previous studies, for the primary outcome of joint swelling, we will use vernier calipers to measure the width and thickness of affected joints, and evaluate the relief of joint swelling using the change of width and thickness. We will also use the visual analogue scale to measure the degree of joint swelling. Measuring joint swelling in these two ways is an innovation different from previous studies. Moreover, the intervention and control of this study are only Qingpeng ointment and placebo ointment. Therefore, in order to improve the compliance of participants, we chose DSSRT as a rescue medicine. Participants in both treatment group and control group can take rescue medicine when the VAS score of joint pain is ≥ 7 points, to relieve the pain. In this way, the compliance of participants can be improved, and the dropout rate of this study can be reduced. After the treatment period, the remaining amount of Qingpeng ointment/placebo ointment will be recorded to assess the compliance of participants to the treatment regimen, and the remaining amount of rescue medicine will also be used as a secondary outcome for evaluating the efficacy of Qingpeng ointment.

The limitation of this study is that the only intervention and control drug are Qingpeng ointment and placebo ointment. Patients with AGA may experience very severe joint pain. The compliance of participants may be affected, if only externally applied drugs are given. In order to improve the compliance of participants, DSSRT will be used as rescue medicine. The investigators will also explain the study protocol and medication requirements to participants detailedly, to ensure that the participants fully understand how to use the drugs. During the treatment period, participants will be instructed regularly to apply the drug on time, and come back to hospital for follow-up.

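### The secondary rescue outcome counts only leftover trial diclofenac, so a patient who takes another flare drug instead scores the same as one who needed nothing

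*Protocol article*

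**What the plan says.** The Secondary outcomes section of the protocol article lists "the remaining amount of rescue medicine at treatment completion" and then gives its timing: "Remaining amount of rescue medicine: Will be recorded after 7 days of treatment". The Discussion states its purpose: "the remaining amount of rescue medicine will also be used as a secondary outcome for evaluating the efficacy of Qingpeng ointment". The Abstract calls the same outcome "the use of rescue medicine as well as adverse effect".

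The Rescue medicine section makes DSSRT the only rescue drug. The pack is given as "specification: 75mg/tablet, 10 tablets/box", and Allocation concealment and blinding puts one such box in each patient's drug box. DSSRT is recommended only while self-scored pain is 7 or more on the 0 to 10 scale. The recommended dose is one tablet a day, and "the maximum dose is one tablet per time, twice a day".

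Other drugs are collected but not used in this outcome. Under Treatment visit, "The combined medication and adverse events during treatment period will be recorded", at the same visit at which leftover rescue tablets are counted. A diary is also kept: under Treatment period, symptom scores "will be scored and recorded on patient diary every day by patients".

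**The concern.** A rescue outcome is meant to show whether patients on the ointment needed less additional treatment than patients on placebo. A count of one returned product shows that only if everyone who needs more treatment takes that product. Here a patient who turns to a different anti-inflammatory drug gets the best possible score.

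Such use is conceivable in this trial. Patients enter with pain of 3 or more, but DSSRT is recommended only at 7 or more, so those scoring below 7 are advised to take no trial oral drug. The Background names colchicine, NSAIDs and glucocorticoids as first-line treatment for this condition, and the Discussion concedes that compliance may suffer when only a topical product is given. What is at stake is the meaning of one secondary efficacy outcome: two quite different clinical courses become indistinguishable in it.

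**Working it through.** The plan gives no sample size, power or expected value for the rescue outcome, so there is no figure to reproduce. The check sets the definition against the supply and dosing rules.

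**Inputs.** Supply: 1 box of 10 tablets, with no resupply described (Rescue medicine; Allocation concealment and blinding). Recommended dose 1 a day, maximum 2 a day (Rescue medicine). Treatment: 7 days (Treatment period). Outcome: tablets remaining after 7 days (Secondary outcomes).

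**Step 1: what the score can distinguish.** Remaining = 10 − trial DSSRT taken.

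| Patient over 7 days | Remaining | Any additional flare drug |
|---|---|---|
| Needs nothing | 10 − 0 = 10 | No |
| Takes colchicine, a steroid or another NSAID, no DSSRT | 10 − 0 = 10 | Yes |
| Takes 1 DSSRT daily | 10 − 7 = 3 | Yes |
| Takes 2 DSSRT daily until the box is empty | 10 − 10 = 0 | Yes |

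The first two rows have the same score but different answers in the last column. The tablet count plus the combined medication record separates them.

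**Step 2: does the supply cover the permitted dose?** Recommended: 1 x 7 = 7, within 10. Maximum: 2 x 7 = 14, and 14 − 10 = 4 tablets are not supplied. At the maximum the box lasts 10 / 2 = 5 days.

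**Step 3: when does that limit bind?** With d two-tablet days and one tablet on each other day, the total is 2d + (7 − d) = 7 + d. For d = 3 this is 10, which the box covers and the count scores correctly. For d = 4, 5, 6 or 7 it is 11, 12, 13 or 14, and all of these read as 0 remaining. With daily use, then, the limit binds only from four two-tablet days upward.

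**Step 4: size.** A bias in the between-group comparison would need the number of patients per arm who take another drug, and how much DSSRT each would otherwise have taken. The documents give neither. For a patient whose pain stays between 3 and 6, the rescue rule implies no DSSRT in any case, so 10 remaining is the correct DSSRT count. What is missed is that the patient still needed a drug. A shift in mean tablets cannot be derived from such patients.

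**The case against.** The strongest reply is that this is a condensed article. Other drugs are recorded, and an analysis plan that is not shown may combine that record with the tablet count. The full protocol may also bar other flare drugs, which would reduce their use to protocol deviations. Part of this stands. It would be wrong to infer that other flare drugs are allowed merely because the article expressly prohibits only other Chinese patent medicines. It would also be wrong to infer that the diary has no daily rescue entry, since the diary is not shown. But the measure itself is stated, not omitted: it is defined as leftover tablets and given an efficacy role. A patient who breaks a prohibition would still receive the best score.

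A reader might also infer that the Abstract contradicts the Methods. It does not: with a fixed supply, use of the trial tablets is 10 minus the remainder, and the Abstract's phrase is a fair shorthand for that.

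On supply, a reader might say that the count fails to register use up to 14. That goes too far. A patient given 10 trial tablets cannot take 14 of them, so all use of the supplied tablets is visible. Only unmet need above 10 is lost, and the recommended dose leaves a margin of 3 tablets. If the comparison is rank-based, which the plan's non-parametric option may mean, patients at the limit still rank as the heaviest users, and only differences among them disappear.

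**Conclusion.** The concern holds for the outcome's definition. Leftover DSSRT does not separate patients who needed no rescue from patients who took something else, although the data that would separate them are already collected. It is a modest but worthwhile correction to one secondary outcome. The supply limit is a minor note.

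The conclusion rests on the text of the definition and the supply arithmetic; no assumption about frequency is needed for it. How many patients are affected is unknown, so no size of bias is given. A reader might infer that the rescue comparison is pulled towards no difference. That would require other-drug use, or running out, to be commoner on placebo, and the documents do not say so. A reader might also infer a consequence for the primary pain and swelling comparisons. Its direction cannot be derived: other drugs could narrow a difference, while patients who run out and take nothing could widen one. None is claimed.

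**What to change.** Before unblinding, define the rescue outcome as yes/no: any DSSRT taken (fewer than 10 tablets returned), or any non-trial analgesic or anti-inflammatory drug, including colchicine and glucocorticoids, during the 7 treatment days. Take it from the tablet count and the combined medication record. Compare the groups by the chi-square test that the Statistical analysis section already plans for categorical data. Keep the leftover count as a descriptive measure.

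For patients still to be enrolled, state what to do if the box runs out before day 7. Supplying more tablets is less simple than it sounds: the 206 boxes had already been packed, recruitment had begun, and the product comes in boxes of 10, so covering 14 means a second or split box.

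The cost is a little more coding of concomitant drugs, done blind to group, plus the ethics and registry notice that the Ethics section requires for any amendment. A yes/no outcome also loses the amount used, which is why the count should still be reported. The redefinition needs no new visits, no larger sample and no change to the primary outcomes, and it works for patients already treated.
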